#### Interim analyses {21b}

Not applicable. Interim testing will not be conducted in this study.

#### Methods for additional analyses (e.g. subgroup analyses) {20b}

Not applicable. No subgroup will be established in this study.

#### Methods in analysis to handle protocol non-adherence and any statistical methods to handle missing data {20c}

An intention-to-treat analysis will be conducted according to the original group allocation. If any participant withdraws from the trial, the last observation carried forward method and multiple imputation method will be respectively carried out to adjust for the missing data.

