**Methods:**

We will conduct a prospective, single-blind randomised controlled trail on 120 older adults with fall risk. Participants will be randomly assigned to an intrinsic-foot-muscle exercise combining the lower extremity resistance training group (IFM group), an extrinsic-foot-muscle exercise combining the lower extremity resistance training group (EFM group) and a control group. The control group will perform lower extremity resistance training. The IFM and EFM groups will be given additional short-foot exercise or towel-curl exercise training, respectively. After the intervention, participants will be followed up for another 12 weeks with no active intervention. The outcome measures will include the postural stability measurements, self-reported postural stability, number of falls, intrinsic-foot-muscle strength and foot arch function. Furthermore, adverse events will be recorded and analysed. If any participant withdraws from the trial, an intention-to-treat analysis will be performed.

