### Additional consent provisions for collection and use of participant data and biological specimens {26b}

No biological samples will be obtained to be stored for use in this study. Additionally, the participants will be asked for permission of the continued use of their data in case of withdrawal from the trial or relevant studies in the future.

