### Criteria for discontinuing or modifying allocated interventions {11b}

Withdrawal from the study will be allowed on the following:
The subject makes such a request.The subject develops a serious disease, such as heart disease or stroke. He or she is unsuitable to continue the participation after the determination of the main investigator.The subject reports serious adverse events in this study. Serious adverse events refer to the unexpected events that may require medical or surgical intervention, such as musculoskeletal problems.

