### Statistical methods

#### Statistical methods for primary and secondary outcomes {20a}

The full analysis set includes all randomised participants who take at least one session of intervention. If follow-up data of primary outcomes are missing, last observation carried forward method and multiple imputation method will be carried out to adjust for the missing data and intention-to-treat analysis was utilised.

The statistical analyses, including calculation of the mean and standard deviation, will be performed using SPSS statistical software (version 20.0 for Windows; SPSS, Inc., Chicago, USA). Descriptive statistics will be used separately for every group and for the total sample. Continuous variables will be presented as means, standard deviation, and 95% confidence intervals. And categorical variables will be expressed percentages and absolute numbers. The normality of distribution for quantitative data will be assessed using the Kolmogorov–Smirnov test. Chi-squared tests or Fisher’s exact tests (categorical variables) and one-way ANOVA or nonparametric tests (continuous variables) will be used respectively to test the demographic differences among the IFM, EFM and control groups.

The average effects (difference between the three groups) for all the variables will be estimated using general linear models of multivariate of analysis for repeated measurements (MANOVA) test, which incorporates the three intervention groups (control * IFM * EFM), time (baseline * post-intervention * follow-up) and group-time interaction. To examine the effect size of the treatment, the partial eta squared will be calculated. Bonferroni’s post hoc test will be applied to identify the differences. Once the significant difference of group-time interaction is detected, the one-way repeated measurements will be performed to determine the difference of effect within each group (pre-intervention, post-intervention and follow-up). Statistical significance will be set at 0.05 for all analyses. Analysis will be carried out by an independent researcher.

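### The analysis set drops randomised participants who never train, against the intention-to-treat promise, and last observation carried forward and multiple imputation are both planned with neither named as primary

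*Protocol article*

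**What the plan says.** **Principle.** Section {20c} of the protocol article states: "An intention-to-treat analysis will be conducted according to the original group allocation". The abstract ties this to drop-out: "If any participant withdraws from the trial, an intention-to-treat analysis will be performed".

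**Analysis set.** Section {20a} states: "The full analysis set includes all randomised participants who take at least one session of intervention".

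**Missing data.** Section {20a} says that, where primary-outcome follow-up is missing, "last observation carried forward method and multiple imputation method will be carried out to adjust for the missing data and intention-to-treat analysis was utilised". Section {20c} says that, for anyone who withdraws, "the last observation carried forward method and multiple imputation method will be respectively carried out to adjust for the missing data". No section ranks the two methods.

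**Stopping.** Section {11b} is headed as covering discontinuation or modification of the intervention, but its text opens: "Withdrawal from the study will be allowed on the following". It then lists a participant's request, serious disease and serious adverse events. Section {26b} adds that "the participants will be asked for permission of the continued use of their data in case of withdrawal from the trial".

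**The concern.** A randomised person who attends no session belongs to an intention-to-treat analysis by allocation but lies outside the full analysis set. The exclusion happens after randomisation. Section {17a} blinds the outcome assessors and analysts and asks participants not to reveal what they receive, so participants know their programme. Not starting could therefore depend on the arm, and the groups compared would no longer be exactly those that were randomised.

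The second problem is that two methods for the same missing values produce two sets of results, and the article does not say which one counts. One of the two fits this design poorly. All three arms do supervised resistance training, so improvement is expected in each. LOCF gives anyone lost before week 12 a gain of zero. For anyone lost later, it puts the value from the end of supervised training in place of the week-24 value that the follow-up phase is meant to measure.

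**Working it through.** **1. The plan's own sample size.** Inputs from section {14}: three groups, α = 0.05, power 0.80, effect size 0.25, result 98 in total. With three time points (section {20a}) I take the group-by-time interaction in a repeated-measures MANOVA (Pillai's trace) and enter 0.25 as the effect size f. With s = 2:

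- df1 = 2 × 2 = 4
- df2 = 2 × (98 − 3 − 2 + 2) = 190
- λ = N·s·f² = 98 × 2 × 0.0625 = 12.25

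Power is 0.8005, and 98 is the smallest N that reaches 0.80, so the figure reproduces. Recruitment of 3 × 40 = 120 implies a loss allowance of 1 − 98/120 = 22/120 = 18.3%. The article does not state a drop-out rate.

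**2. Never-starters and power.** Their number is not in the document. If 0%, 5% or 10% of the 120 never start, the full analysis set is 120, 114 or 108, and power at the plan's own effect size is 0.884, 0.865 or 0.843. Power is therefore not the issue. The issue is the contradiction between {20a} and {20c}, and the possible bias from excluding people after allocation.

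**3. The two missing-data statements side by side.** Section {20a} is triggered by missing follow-up of primary outcomes, and section {20c} by any withdrawal. Both name LOCF and multiple imputation. In {20c} the word *respectively* would need two situations to match the two methods, but only one is given. No reading of either section yields a single primary method.

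**4. What LOCF does.** The inputs below are assumptions, apart from 18.3%, which comes from step 1. Gains are 1.0 SD (IFM) and 0.5 SD (control), all loss occurs before week 12, and drop-outs would have gained as much as completers. The true difference is 1.0 − 0.5 = 0.50 SD. With loss fractions d_IFM and d_C:

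LOCF difference = 1.0 × (1 − d_IFM) − 0.5 × (1 − d_C)

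| Loss IFM | Loss control | LOCF difference (SD) | Bias (SD) |
|---|---|---|---|
| 18.3% | 18.3% | 0.817 − 0.408 = 0.41 | −0.09 |
| 25% | 10% | 0.750 − 0.450 = 0.30 | −0.20 |
| 10% | 25% | 0.900 − 0.375 = 0.525 | +0.025 |

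If both arms truly gain 0.5 SD, losses of 25% and 10% give 0.5 × (0.75 − 0.90) = −0.075 SD where the true difference is zero.

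**5. Relaxing the drop-out assumption.** Suppose drop-outs would have achieved a fraction g of the completers' gain. Then:

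Bias = −g × (1.0 × d_IFM − 0.5 × d_C)

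At g = 1 this returns the table. At g = 0.5 the three biases halve to about −0.05, −0.10 and +0.0125 SD. At g = 0 they vanish.

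**6. Loss after week 12.** LOCF then leaves the week-12 comparison untouched and affects only week 24. The document gives no basis for predicting the direction.

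**The case against.** **Never-starters may be few.** Eligibility requires availability three times a week for 12 weeks, and every arm receives the same resistance training, so there is no untreated arm to refuse. That stands as a reason to expect a small effect. It does not remove the contradiction.

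**The illustration rests on chosen numbers.** This also stands. The gains and the unequal losses are assumptions, all loss is placed before week 12, and step 5 shows that the bias shrinks if drop-outs would have gained less. No gap between LOCF and multiple imputation has been calculated. What survives is that LOCF can err in either direction and so cannot be defended as conservative.

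**A separate analysis plan could rank the methods.** It could. But the article does more than leave the ranking open. It states that both methods will be carried out, and it states a one-session condition that a later plan would have to contradict.

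**Stronger readings that the document does not support.**

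- A reader might infer from {11b} that everyone who stops training leaves the study and gives no week-12 or week-24 data. The wording is permissive, covers listed reasons only and says nothing about missed sessions. The sections on follow-up after intervention, {11c} and {18b} bring participants back for assessment without exception, and {26b} seeks continued use of data after withdrawal.
- A reader might conclude that intention-to-treat is abandoned altogether. Analysis by allocated arm with imputation for withdrawals is planned, and only never-starters are certainly excluded.
- A reader might compute √(98/120) = 0.90 and say that LOCF makes standard errors 10% too small. That ignores how carried-forward values change the outcome variance, so it is not a result for this analysis.

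**Conclusion.** The concern holds on two stated rules. The one-session condition in {20a} contradicts the promise in {20c} to analyse by original allocation. LOCF and multiple imputation are both prescribed without a primary, so the main result is not fixed in advance.

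Under the assumptions in step 4, LOCF turns a true 0.50 SD into anything from 0.30 to 0.525 SD across the three loss patterns shown, and less bias follows if drop-outs would have gained less. The size of the never-starter effect cannot be derived from the document.

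A secondary point is that {11b} does not separate stopping the intervention from leaving the study, so assessment after stopping is not secured. It goes no further than that.

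**What to change.** - In {20a}, define the primary analysis set as all randomised participants in their allocated arm, and remove the one-session condition.
- In {20a} and {20c}, name one primary approach in the same words. The multiple imputation already planned is enough. A likelihood-based mixed model on all observed visits is an acceptable alternative, but changing the model is optional.
- Drop LOCF, or label it a sensitivity analysis only.
- In {11b}, distinguish stopping the intervention from leaving the study, and state that those who stop training are still invited, with consent, to the scheduled week-12 and week-24 assessments. This concerns data collection only and changes no rule on when training should stop.

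The cost is wording plus a few visits already in the schedule. The small downside is some dilution of the effect from including never-starters. The changes should be settled before anyone sees outcome data by arm.

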#### Plans to give access to the full protocol, participant-level data and statistical code {31c}

The datasets analysed during the current study are available from the corresponding author on reasonable request.

### Oversight and monitoring

#### Composition of the coordinating centre and trial steering committee {5d}

The trail steering committee will be formed up of two main investigators in this study, the coordinating centre and the administrative staff of funding. In addition, the group of coordinating centre will be formed up of teachers in Sport Medicine and Rehabilitation Centre, Shanghai University of Sport, and the administrative staffs in community centres.

#### Composition of the data monitoring committee, its role and reporting structure {21a}

The main investigator will email the ethics committee of the University about adverse events or any other changes in the trial. Additionally, after the trial, the main investigator will report the results, adverse event log and publication to the funding committee.

#### Adverse event reporting and harms {22}

The interventions that involve strength training will be performed under the supervision of the qualified physical therapist. Even during the follow-up period, the guidance will be provided weekly for the security of home-based interventions. All participants will be instructed to report any abnormal reactions or uncomfortable feelings experienced to any researcher. Additionally, all adverse events will be recorded truthfully in the trial. The physical therapist and outcome assessors will also collect and record adverse events or any other unintended effects during the interventions and laboratory test, such as musculoskeletal problems (i.e. muscle strain or joint pain). These results will be reported to the main investigator in weekly research meetings.

#### Frequency and plans for auditing trial conduct {23}

The Project Management Group will report the study progress in the form of weekly research meetings. Meanwhile, the Trial Steering Group and Ethics Committee will meet monthly to review conduct throughout the trial period. Due to the low-risk intervention conducted in this study, it is not necessary to make plans to consider a Data Monitoring Committee.

#### Plans for communicating important protocol amendments to relevant parties (e.g. trial participants, ethical committees) {25}

Any important protocol modifications, including the principal investigator, informed consent form, study protocol regarding eligibility criteria, outcomes and analyses, will be reported to all investigators, trial participants, trial registry and ethics committee of the university.

### Dissemination plans {31a}

The results will be reported in conferences or peer-reviewed journals. The results will also be shared with participants, healthcare professionals and the public through lectures or science handbooks.

## Discussion

Falls, as a major public health issue, negatively affect the quality of life, physical function, mental health and social connectedness of older adults, resulting in significant economic burden experienced by themselves, their families, healthcare providers and the healthcare system [41]. As a direct interface between the body and the ground, the human foot contributes to postural stability in most static postures and dynamic activities [13].

Recently, with the development of foot and ankle biomechanics, intrinsic foot muscles have been found to play an active role in foot core stability [15], which is associated with postural stability [19–21]. Kelly et al. [42] assessed the electromyography data of the healthy male participants while performing two quiet standing postures with varying degrees of difficulty (double- and single-leg stances). They found that the activation of the plantar intrinsic foot muscles (the abductor hallucis, flexor digitorum brevis and quadratus plantae muscles) increased with increasing postural demand, and these intrinsic muscles were recruited in a highly coordinated manner to stabilise the foot and maintain balance in the medio-lateral direction. Further research found that the recruitment of these muscles was positively associated with the postural sway of a single-leg stance task [20]. In another biomechanical study, healthy young individuals were instructed to perform an exercise to fatigue the toe and ankle plantar flexors. Their postural control variables were altered after the fatiguing exercises.

Integrating intrinsic-foot-muscle exercises within the lower extremity resistance training, which has been considered as the effective management of fall, is a novel approach. However, this exercise has demonstrated feasibility and effectiveness in the clinical setting among healthy adults and individuals with ankle instability [25, 26]. However, limited research has explored the relationship between intrinsic-foot-muscle function and postural control in older adults. Furthermore, clinical research that investigates the effectiveness of this intervention on postural control in the elderly is lacking.

In conclusion, this protocol will be conducted as a randomised clinical trial and will investigate the efficacy of a 12-week intrinsic foot muscle training combined with lower extremity resistance training on postural stability outcomes in elderly people with fall risk. In this study, we will test the comprehensive outcomes of postural stability during participants walking, static standing and standing under external disturbance. Furthermore, the function of intrinsic foot muscles to support the arch will be evaluated by several quantified tests. The proposed work has the potential to advance the field of elderly fall rehabilitation management by integrating intrinsic-foot-muscle exercise into a lower extremity resistance intervention that will improve foot function and postural stability and ultimately promote balance confidence. The results of this study will determine the effectiveness and provide scientific evidence to establish comprehensive fall prevention intervention.

## Trial status

Protocol: version 2.0; data 31 December 2020.

Date of recruitment began on 1 February 2021.

Date of recruitment will be completed on 31 December 2021.

## Abbreviations

IFM: Intrinsic-foot-muscle exercise
EFM: Extrinsic-foot-muscle exercise
SF: Short-foot
TC: Towel-curl
COP: Centre of pressure
TUG: The Timed Up and Go
ML: Medial-lateral
AP: Anterior-posterior
TL: Total length
SA: Sway area
COG: Center of gravity
SOT: Sensory organisation test
LOS: Limits of stability test
